**3.4. Sampling**

Musina municipality will be purposefully selected from Vhembe District. These are in geographic proximity of the University of Venda where researcher is located and where the previous study was conducted ([name] *et al*., 2015). Simple random sampling will be used to select six preschools, three each from the two local municipalities. Simple random sampling is a sampling procedure, which provides equal opportunity of selection for each element in a population (Lee and Nieman, 2010). A list of pre-schools will be obtained from the Department of Social Development in Vhembe district and each pre-school will be assigned a number. The researcher will randomly select one number at a time. The following Slovin formula is used to calculate the total sample size used in the study: n = N/ (1 + (N X e^2^)) where

n= sample size

N= total number of children in the pre-schools; and

e = the accepted level of error

n = N/ (1 + (N X e^2^))

=40291/ (1+(40291 x 0.05)

=40291/ 101.7275.

= 396

= plus 10%

= 435.6

= 436

The formula yielded 396 participants, and an additional 10% will be added to account for attrition, making 436. Total sample size was calculated from the total number of children registered in the Early Childhood Development under Social Development in South Africa in 2017 in Vhembe district (Government Gazette, 2017). The sample frame will be six preschools, which are yet to be randomly selected. If the total number of participants in these six selected preschools does not reach the total number of 436, two more preschools will be added to the sample frame. The six preschools will be randomly assigned to the treatment or control.

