***Dietary patterns***

The 24-hour recall will be analysed using the 11-food item to determine dietary diversity score. The FFQ will be analysed using SPSS version 23 for frequencies as daily, weekly, monthly, seasonal or never. Consumption of indigenous foods will be determined using frequencies. Food finder (MRC) will also be used to analyse the nutrient intakes.

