**3.6.4.4. Measurements, procedures and analysis**

The following measurements will be done: demographic and environmental factors, anthropometrics, dietary intakes and patterns, and biochemical data. Same parameters and procedures, which were done at the baseline and described in section 3.6.2.4, will be followed. Data will be analysed using same procedures as described for baseline, with addition regression and ANOVA to measure changes from baseline to post intervention, and between experimental and control. See table 3.5 below. This is done to determine the changes in nutritional status that is likely to have occurred because of the intervention. A statistician will be consulted.

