**Table 3.5: Proposed data analysis table**

| **Descriptive Statistics** | **Categorical data** | **Numerical data** | |
| --- | --- | --- | --- |
|  |  | **Normally distributed** | **Non-normally distributed** |
| ***Socio demographic information***   - Age - Gender   ***Anthropometric measures***   - Weight, height, MUAC - Categorization according to Z-scores: height for age, weight for age and BMI for age   ***Nutrient intake from 24hr recall***   - Total intake, - Consumption pattern   ***Dietary patterns***  Frequency of inclusion of food item in the FFQ  Morbidity diary  **Biochemical measures**   - Serum zinc - haemoglobin - Serum Ferritin - C-reactive protein - Transferrin saturation - Serum ferritin | Frequencies n (%) | Mean $\pm$ SD | Median and IQR |
| ***Analytical statistics-*** |  |  |  |
| ***Comparison of micronutrient status by subject characteristics*** | Pearson’s Chi-square test/Fishers exact test | ANOVA/T-test | Kruskal-Wallis/Mann-Whitney U tests |
| ***Association between dietary intakes and micronutrient status*** | Regression analyses with dietary intakes and anthropometric indices as dependent variables and all other as independent | | |
| ***Validation of dietary intake and micronutrient status against the intervention*** | Spearman’s correlation coefficient  Comparison of means/means Weighted kappa statistic for agreement testing  Bland Altman plots for bias and agreement testing | | |

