**APPENDIX: D**

**SELECTED FOOD FREQUENCY QUESTIONNAIRE**

|  |  | **Average use** | | | | | | | |
| --- | --- | --- | --- | --- | --- | --- | --- | --- | --- |
| **Code** | **Food items** | **<1 month** | **1-3**  **Month** | **1 week** | **2-4**  **week** | **5-6**  **week** | **1 day** | **2-3**  **day** | **4+**  **day** |
| **Starchy food** | | | | | | | | | |
| **50** | Stiff MM porridge |  |  |  |  |  |  |  |  |
| **51** | Soft MM porridge |  |  |  |  |  |  |  |  |
| **52** | Fermented Soft MM porridge |  |  |  |  |  |  |  |  |
| **53** | Fermented Stiff MM porridge |  |  |  |  |  |  |  |  |
| **54** | Fermented home-made soft porridge |  |  |  |  |  |  |  |  |
| **55** | Samp |  |  |  |  |  |  |  |  |
|  | Rice |  |  |  |  |  |  |  |  |
|  | Macaroni |  |  |  |  |  |  |  |  |
|  | Spaghetti |  |  |  |  |  |  |  |  |
|  | Cooked maize cob |  |  |  |  |  |  |  |  |
|  | Roasted maize cob |  |  |  |  |  |  |  |  |
|  | Oats porridge |  |  |  |  |  |  |  |  |
|  | Muesli |  |  |  |  |  |  |  |  |
|  | Cornflakes |  |  |  |  |  |  |  |  |
|  | All bran |  |  |  |  |  |  |  |  |
|  | Brown Bread |  |  |  |  |  |  |  |  |
|  | Whole wheat bread |  |  |  |  |  |  |  |  |
|  | White bread |  |  |  |  |  |  |  |  |
|  | Home-made bread |  |  |  |  |  |  |  |  |
|  | Dumpling |  |  |  |  |  |  |  |  |
|  | Fat-cakes |  |  |  |  |  |  |  |  |
|  | Scones |  |  |  |  |  |  |  |  |
|  | Cakes |  |  |  |  |  |  |  |  |
|  | Muffins |  |  |  |  |  |  |  |  |
|  | Biscuits |  |  |  |  |  |  |  |  |
| **Protein foods (Meat and meat product)** | | | | | | | | | |
|  | Chicken drumstick (F/S) |  |  |  |  |  |  |  |  |
|  | Chicken thigh (F/S) |  |  |  |  |  |  |  |  |
|  | Chicken breast (F/S) |  |  |  |  |  |  |  |  |
|  | Chicken wing (F/S) |  |  |  |  |  |  |  |  |
|  | Stewed chicken feet |  |  |  |  |  |  |  |  |
|  | Chicken heads |  |  |  |  |  |  |  |  |
|  | Chicken liver |  |  |  |  |  |  |  |  |
|  | Chicken gizzard |  |  |  |  |  |  |  |  |
|  | Chicken necks |  |  |  |  |  |  |  |  |
|  | Chicken giblets |  |  |  |  |  |  |  |  |
|  | Stewed chicken |  |  |  |  |  |  |  |  |
|  | Barbequed/grilled chicken |  |  |  |  |  |  |  |  |
|  | Braai or dusty chicken |  |  |  |  |  |  |  |  |
|  | Stewed Turkey |  |  |  |  |  |  |  |  |
|  | Beef stew |  |  |  |  |  |  |  |  |
|  | Braai beef |  |  |  |  |  |  |  |  |
|  | minced meat |  |  |  |  |  |  |  |  |
|  | Ox Tripe |  |  |  |  |  |  |  |  |
|  | Ox Liver |  |  |  |  |  |  |  |  |

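### The open-ended predictor rule in Table 3.5 admits post-intervention markers, the raw inputs of z-scores and possibly up to 228 food items; a short named list should replace it

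*Protocol*

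**What the plan says.** In the protocol's Table 3.5, the row headed "Association between dietary intakes and micronutrient status" specifies "Regression analyses with dietary intakes and anthropometric indices as dependent variables and all other as independent". It gives no variable list, no limit on their number, no selection rule, and no statement whether baseline or post-feeding values are meant. It is the only row of the table that names regression.

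Section 3.6.4.4 covers the post-feeding phase. It repeats the baseline procedures "with addition regression and ANOVA to measure changes from baseline to post intervention", extends this to the comparison of experimental and control groups, and refers the reader to Table 3.5. It adds that a statistician will be consulted.

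The descriptive block of Table 3.5 shows which variables are available:
- age and gender;
- weight, height and MUAC, and z-score categories;
- nutrient intake from the 24-hour recall;
- under a separate dietary-patterns heading, "Frequency of inclusion of food item in the FFQ";
- a morbidity diary;
- serum zinc, haemoglobin, ferritin (listed twice), C-reactive protein and transferrin saturation.

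The food-frequency form is Appendix D ("SELECTED FOOD FREQUENCY QUESTIONNAIRE"). The dietary-patterns paragraph of the phase-two analysis says: "The FFQ will be analysed using SPSS version 23 for frequencies as daily, weekly, monthly, seasonal or never". The opening paragraph of that same analysis section, however, includes FFQ data among those to be handled with several methods, regression being one.

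Section 3.4 gives the sample size: "The formula yielded 396 participants, and an additional 10% will be added to account for attrition, making 436".

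**The concern.** A protocol may leave covariates to a later analysis plan. This one does not leave them open: it fixes a rule, and the rule is everything else. Three consequences follow.

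- **Adjustment for consequences of treatment.** Zinc, ferritin and haemoglobin are measured again after feeding and fall on the predictor side. An arm coefficient in such a model is no longer the effect of allocation.
- **Built-in association.** Raw weight, height, age and sex can predict the growth indices derived from them. A high R² there says nothing about nutrition.
- **No cap.** Nothing stops many questionnaire items from entering at once. In an over-filled model the raw R² looks impressive, and some foods appear significant by chance alone.

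At stake is whether a reported regression can be interpreted. A thesis chapter or paper that lists significant foods, or an adjusted arm effect, from such a model would mislead.

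**Working it through.** **1. The plan's own sample size.** Section 3.4 prints "40291/ 101.7275". The denominator is 1 + 40291 × 0.05² = 1 + 40291 × 0.0025 = 101.7275, and 40291/101.7275 = 396.07, so 396. Adding 10%: 396 × 1.10 = 435.6, so 436. Both figures reproduce. (One printed line omits the square on 0.05; the denominator includes it.) The feeding-trial schematic in section 3.6.3 implies a different total, 8 × 73 = 584, which is used below as a sensitivity value.

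**2. Post-intervention markers beside arm.** Section 3.6.4.4 needs an arm term for its between-group use and refers to Table 3.5. The rule there adds every variable that is not an outcome, which includes the post-feeding markers. In a linear model, let T be the total effect of arm on outcome Y, d the effect of arm on marker M, and c the coefficient of M given arm. The arm coefficient with M in the model is then b = T − c·d. The better the feeding works on M (larger d), the more is taken out of b whenever c is not zero. The protocol gives neither c nor d, so the size cannot be computed. In the row as printed, Y is a dietary or anthropometric variable; zinc and iron status are never the outcome.

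**3. Indices and their inputs.** The row names anthropometric indices as outcomes. Table 3.5 also lists raw weight and height, plus age and gender, and the phase-two anthropometrics paragraph obtains weight-for-age, height-for-age and weight-for-height z-scores with the WHO software. Weight-for-age regressed on weight, age and sex is close to an identity.

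**4. Count of FFQ items in Appendix D.** Starchy 25 + protein 40 + milk 18 + legumes 25 + fruits 33 + vegetables 74 + beverages 13 = 228.

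**5. Chance fit.** With p predictors unrelated to the outcome and n independent children, expected R² = p/(n − 1), and the expected number of coefficients with p<0.05 is 0.05p. The protocol states no alpha; two-sided 0.05 is assumed.

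| Reading | p | n | Expected R² | Children per predictor | Chance p<0.05 |
|---|---|---|---|---|---|
| All FFQ items entered singly | 228 | 396 | 228/395 = 0.577 | 1.7 | 11.4 |
| Many questionnaire items (assumed number) | 100 | 396 | 100/395 = 0.253 | 4.0 | 5.0 |
| FFQ counted as dietary intake; other Table 3.5 variables only | 8 | 396 | 8/395 = 0.020 | 49.5 | 0.4 |
| All FFQ items, children as in the feeding schematic | 228 | 584 | 228/583 = 0.391 | 2.6 | 11.4 |

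The 8 are age, gender, morbidity, zinc, haemoglobin, ferritin, C-reactive protein and transferrin saturation.

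**6. Simulation check.** Over 600 runs of independent normal data with n = 396 and p = 228, mean R² was 0.577, mean adjusted R² was −0.001, and 11.3 coefficients on average had p<0.05. The overall F test rejected in 6.0% of runs. The simulation error at 5% is √(0.05 × 0.95/600) = 0.9 percentage points, so 6.0% is compatible with the nominal level.

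**The case against.** The strongest objection is that the sentence itself puts dietary intakes and anthropometric indices on the dependent side. FFQ data are dietary data: section 3.6.2.5 collects the recall and the FFQ under one heading, and the dietary-patterns paragraph plans frequencies for the FFQ. On that reading the predictors are about 8 variables and over-fitting is negligible. This stands as a legitimate reading. It is not the only one, because Table 3.5 separates recall intake from FFQ patterns, and the phase-two analysis paragraph lists FFQ data among those open to regression.

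A reader might infer that the row, as written, means at least 228 predictors and will show strong associations where none exist. The documents do not support that. No sentence enters single foods in a model. Even with all 228, only raw R² and the count of chance-significant coefficients grow; adjusted R² stays near zero, the F test keeps its level under independence, and 11 in 228 is simply the nominal 5%. Entering each FFQ column as a category would be a further assumption, since the stated analysis uses five frequency classes.

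It can also be said that the row describes an association, that arm is not named in it, and that covariates may be settled in an analysis plan not shown. The first two are true, so the bias in an arm effect is conditional on arm being in the model. But section 3.6.4.4 wants a between-group regression and points to a table with only this one. The third does not excuse a rule that the protocol has already fixed. Finally, if indices is read loosely enough to cover raw weight and height, the near-identity disappears; the table, however, lists raw measures and z-scores as separate entries.

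**Conclusion.** The point holds in a limited form: the stated predictor rule is a poor one and cannot be followed literally with interpretable results. Two defects do not depend on how the FFQ is classified. One is adjustment of any arm term for post-intervention markers, whose size the documents do not allow one to compute. The other is the regression of growth indices on their own raw inputs.

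The over-fitting part is conditional. For 396 children, chance R² runs from about 0.02 (about 8 predictors, 0.4 false positives) to about 0.58 (228 predictors, about 11 false positives); with 584 children the upper figure is 0.39. These figures assume independent observations, predictors unrelated to the outcome, one column per food, and two-sided alpha 0.05. Clustering by preschool is not in them. They do not show that the trial's efficacy comparison is wrong.

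**What to change.** Replace the all-other clause in Table 3.5 with a named outcome and a short pre-specified list:

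- Regress each post-intervention marker (serum zinc, haemoglobin, ferritin) on arm, its own baseline value, and baseline age, sex, household income, C-reactive protein and dietary diversity score.
- Account for preschool as the unit of randomisation. The method must suit few clusters: section 3.4 plans six preschools and the feeding schematic shows eight.
- State that no post-intervention biomarker, diet or anthropometric variable enters a model that contains arm. Diet belongs in this rule because section 2.5 expects the nutrition education to change eating patterns.
- State that raw weight and height do not predict indices derived from them.
- Report single FFQ foods descriptively, as the dietary-patterns paragraph already plans.

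All these baseline variables are already collected, so the cost is the wording of one table row. The price is that exploratory associations with single foods are not tested.

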**3.7. Fieldworkers**

Five nutritionists will be recruited for monitoring, implementation of the feeding trial. The researcher will train field workers and methods of data collection will be standardized during piloting. The total team will be six including the researcher. Phlebotomist will be responsible for drawing blood as it is a requirement by the Health Professional Council of South Africa and these will be provided as part of the package from Ampath laboratories. The appointment of fieldworkers will be based on their expertise, which will be required for the study and for good general practice. There will be three teams with each visiting one primary school on the day of the feeding trial for monitoring. The table below illustrates the data collection responsibilities.

**Table 3.6: Personnel responsibilities during data collection**

| **PERSON RESPONSIBLE** | **Phase 1: Development of an intervention** | **Phase 2: Implementation of NE, NSFP meal and dish** | | |
| --- | --- | --- | --- | --- |
|  |  | **Phase Two** | **Phase 3:**  **Implement intervention** | **Phase 4:**  **Evaluate efficacy** |
| Promoters | Quality control | Quality control | Quality control | Quality control |
| Researcher | Recipe development and standardization  Training of field workers  Feedback meetings with promoters and quality control  Transport dishes for nutrient and microbial analysis | Arrange all resources needed for data collection car, equipment, pens etc.  Data collection with field workers  Feedback meetings with promoters and quality control  Data capturing and analysis | Purchasing of ingredients for preparation of Snack  Provide snack for preschools  Provide nutrition education using song  Quality control once every two weeks | Arrange all resources needed for data collection car, equipment, pens etc.  Data collection with field workers  Feedback meetings with promoters and quality control  Data capturing and analysis |
| Field workers  Nutritionist | Form part of the team  Assist in sensory evaluation  Pilot | Anthropometric measurements Questionnaire  Data capturing and cleaning | Intervention implementation Prepare the dishes  Serve the children  Data collection  Compliance  Plate waste studies | Questionnaires  Anthropometric measurements  Data capturing and cleaning |
| Field worker-  Phlebotomist | N/A | Draw blood  Transport to the lab storage and analysis | N/A | Draw blood and transport to the lab for storage and analysis |
| Pre-School teacher/principal | N/A | Subject recruitment  Allocate space | Receive ingredients/food  Monitoring | Participate in monitoring and quality control |

**3.8. Institutional approval**

The research proposal will be submitted to Health Research Ethics committee (HREC) of Stellenbosch University and to the Higher Degrees and Ethics committee of University of Venda for approval prior to data collection. An ethical clearance certificate will be issued, and it will be submitted to the Departments of Health and Social Development provincial department and district office together with the letter requesting permission to conduct research in pre-schools (**Appendix G**). Once permission is granted, a list of pre-schools will be obtained from the Department of Social Development, Vhembe district and the local municipalities will be consulted. Permission to include pre-schools into the sample will be sought with the headmasters and the school governing body.

**3.9. Ethical considerations**

No participants will be enrolled into the study until the protocol, participants’ information sheet and recruitment material are approved in writing by the Ethics Committees of the two Universities. The study will be performed in accordance with principles of the Declaration of Helsinki (2013), Good Clinical Practice and the laws of South Africa. No participants will be entered in the study without signed informed consent by parents after the researcher (see Appendix H) has provided a full and adequate oral and written explanation of the study, including possible risks and benefits. Verbal ascent will be obtained from the children before data collection. Consenting process will be conducted in the local languages (*Tshivenda* and *Xitsonga*) and consent forms will be made available in the same languages. Participants will have the right to withdraw from the study at any time. If in the process of the research a participant is diagnosed with a nutrition-related health risk or disease, the parents/guardian will be informed and referred to appropriate health professional or service to address the problem. Data generated from the study will be stored in a computer database, and in a manner, that maintains participants’ confidentiality. For data verification and quality control, purposes regulatory authorities and/ or members of the Ethics Committee of the Universities might be allowed access to participant data under conditions of strict confidentiality. This will be stated in the patient information sheet. The anonymity of participants will be ensured by using codes instead of names and in any publication of the data.

**3.10 Budget and sources of Income**

**Table 3.7: Proposed budget for the study**

| Item | Description | Unit | Unit price | Actual cost |
| --- | --- | --- | --- | --- |
| *Transport* | **UNIVEN to Polokwane, circuits in Vhembe district, selected preschools, Ampath lab and return (3302KM for data collection of first phase).**  **UNIVEN to selected preschools in Vhembe district (6900KM for 6 months’ data collection of second phase).**  **UNIVEN to selected preschools, Ampath Laboratory at Polokwane (3824KM for data collection of third phase)** | **3302KM**  **6900KM**  **3824KM** | **R3.55** | **R11722.1**  **R146970**  **R13575.2** |
| *Consultation visits at SU* | **Accommodation**  **Return Flight**  **Ground transportation for 5 days x2 trips** | **2**  **2**  **2** | **R1300**  **R5000**  **R3905** | **R16505** |
| *Equipment’s* | **centrifuge machine**  **needles**  **Test tubes**  **alcohol**  **cotton wool swabs.** |  |  | **R52500** |
| *Ampath* | **Package Nurse, blood collection and analysis**  **Full blood count & platelet count**  **Serum iron**  **Ferritin**  **Transferrin**  **CRP**  **Zinc** | **436 x 2** | **152.8**  **80.9**  **148.9**  **140.3**  **130**  **217.6** | **R759076** |
| *Consumables* | **Cucurbita Moschata seeds**  **Cool box**  **Stationary**  **Tape recorder**  **Digital discs or tapes** |  |  | **R18 000** |
| *Field worker* | **Nutritionist (9 months x 4 days per week at 16 days per month)** | **5** | **150 per day^1^** | **R108 000** |
| *Printing and editing* | **Editing (R30) per page**  **Printing of first draft**  **Printing of Second draft**  **Printing of questionnaires (3 pages x400 copies 1500)**  **Printing of final copy (4x80)**  **Binding (4 X R1000)**  **Spiral Binding (4 x R50)** | **80**  **160**  **160**  **2000**  **320**  **4**  **4** | **R30**  **R3**  **R3**  **R3**  **R3**  **R1000**  **R50** | **R14520** |
| *Analysis cost* | **microbial activity, toxicity level, micronutrient content, life span** |  |  | **R60 000** |
| *TOTAL* |  |  |  | **R1 114 668.3** |

**^1^per day value based on UNIVEN rates**

**Table 3.8: Source of Income**

| Source | Amount | Status |
| --- | --- | --- |
| UNIVEN capacity development grant (DHET) | **R300 000.00** | To apply once registered |
| UNIVEN support for research running costs staff registered for PHD | **R100 000.00** | To be accessed once the proposal is approved by Ethics Commitees |
| NRF (THUTHUKA) | R454 662.00 | Allocated /awarded for  2018-2020 |
| Other |  | To be identified with the support of promoters |
| Total | **R554 662.00** | **Available** |

